## Abstract

**Background:**

Current international guidelines recommend the use of a daily topical exit-site antimicrobial to prevent peritoneal dialysis (PD)-related infections. Although nonantibiotic-based therapies are appealing because they may limit antimicrobial resistance, no controlled trials have been conducted to compare topical antimicrobial agents with usual exit-site care for the prevention of PD-related infections among the Thai PD population. We propose a controlled three-arm trial to examine the efficacy and safety of a daily chlorhexidine gluconate-impregnated patch versus mupirocin ointment versus usual exit-site care with normal saline for the prevention of PD-related infections.

**Methods/Designs:**

This study is a randomized, double-blind, multicenter, active-controlled, clinical trial. Adult patients aged 18 years or older who have end-stage kidney disease and are undergoing PD will be enrolled at three PD Centers in Thailand. A total of 354 PD patients will be randomly assigned to either the 2% chlorhexidine gluconate-impregnated patch, mupirocin ointment, or usual exit-site care with normal saline dressing according to a computer-generated random allocation sequence. Participants will be followed until discontinuation of PD or completion of 24 months. The primary study outcomes are time to first PD-related infection (exit-site/tunnel infection or peritonitis) event and the overall difference in PD-related infection rates between study arms. Secondary study outcomes will include (i) the rate of infection-related catheter removal and PD technique failure, (ii) rate of nasal and exit-site *Staphylococcus aureus* colonization, (iii) healthcare costs, and (iv) skin reactions and adverse events. We plan to conduct a cost-utility analysis alongside the trial from the perspectives of patients and society. A Markov simulation model will be used to estimate the total cost and health outcome in terms of quality-adjusted life years (QALYs) over a 20-year time horizon. An incremental cost-effectiveness ratio in Thai Baht and U.S. dollars per QALYs gained will be illustrated. A series of probabilistic sensitivity analyses will be conducted to assess the robustness of the cost-utility analysis findings.

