#### Secondary outcomes

Secondary outcomes include the following:

*Clinical events*
Infection-related catheter removalPD technique failure

*S. aureus colonization*
Incidence of nasal *S. aureus* colonizationIncidence of exit-site *S. aureus* colonization

*Healthcare costs*
Direct medical costs including for the IMPs, non-IMPs and equipment, outpatient and emergency visits, hospitalization, antimicrobial treatment for PD-related infection, laboratory tests and procedures, and costs related to adverse eventsDirect non-medical costs including for transportation and the monetary value of informal careIndirect costs including daily wages of participant and family caregiver for treatment follow-ups and extra visits

*Safety*
Skin reactionsSafety of IMPs related to potential harm (e.g., adverse events, serious adverse events, participant survival in each group, hospitalization, and emergency visits)

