#### Statistical analysis

Baseline characteristics will be summarized as number (percentage) or mean ± standard deviation, or medians with interquartile range as suitable. Differences between treatment groups will be compared using Fisher’s exact test and analysis of covariance (ANCOVA) or Kruskal-Wallis test for categorical and continuous variables, respectively. All analyses will be conducted on both a per-protocol and intention-to-treat basis. All analyses will be performed using Stata software version 14.0 (StataCorp, LP) and Microsoft Excel version 2016. They will be two-tailed, and a *P*-value less than 0.05 will be considered statistically significant.

For a primary analysis, Cox proportional hazards regression and Poisson regression analyses will be performed to assess the effectiveness of the chlorhexidine gluconate-impregnated patch and mupirocin ointment compared to usual exit-site care with normal saline for the first episode of PD-related infection and longitudinal rates, respectively. Secondary analysis using statistical methods as described above will then be analyzed to evaluate the effect on the prevention of PD-related infections between chlorhexidine gluconate-impregnated patch and mupirocin ointment. The treatment effects will be estimated as hazard ratios or incidence rate ratios with corresponding 95% confidence interval. Kaplan-Meier survival curves will be constructed for visual presentation of time-to-event comparisons.

Several a priori subgroup analyses with respect to the minimization variables for both primary and secondary outcomes will be investigated. For instance, the lists of variables include age (<65 vs. ≥65 years), gender, history of diabetes, history of PD-related infections (peritonitis or exit-site/tunnel infection), *S. aureus* colonization status (nasal or exit-site PD catheter), PD modality (continuous ambulatory peritoneal dialysis vs. automated peritoneal dialysis), PD vintage, and serum albumin (< 3.5 vs ≥3.5 mg/dL).

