To address robustness of the treatment effects, further sensitivity analyses of the primary analysis will be performed by (i) adjusting for the several baseline covariates that seem to affect the outcomes (age, history of diabetes, history of PD-related infections, *S. aureus* colonization status, PD modality, PD vintage, and serum albumin); (ii) restricting the analysis to only PD-related infection episodes with positive cultures to account for misclassification bias; (iii) using the proportional sub-distribution hazards analyses by Fine and Gray method to address the completing risk outcomes, including mode switching to long-term hemodialysis, kidney transplantation, conservative treatment, or death; and (iv) using the multiple imputation method to evaluate the effect estimates when missing data are indicated.

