### Study withdrawal

Participants may withdraw from the trial at any time for any reason. Furthermore, participants who meet any of the following conditions will be allowed to withdraw from the trial: (i) refusing to follow the study protocol; (ii) using other IMPs; (iii) pregnancy during the study period; (iv) switching mode to long-term hemodialysis, kidney transplantation, or conservative treatment; and (v) developing serious adverse drug reactions or suspected unexpected serious adverse reactions. According to the intention-to-treat approach, data collected prior to study withdrawal will be considered for participants who discontinue or deviate from the assigned intervention protocols.

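### Follow-up ends when PD ends although participant survival is a safety outcome, so deaths after leaving PD go uncounted and censoring at that point may be informative

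*Protocol article*

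**What the plan says.** The Abstract (Methods/Designs) sets the observation period: "Participants will be followed until discontinuation of PD or completion of 24 months". Under Secondary outcomes, the safety group gives as examples of potential harm "participant survival in each group, hospitalization, and emergency visits". The same trial counts "the rate of infection-related catheter removal and PD technique failure" as secondary outcomes, so one trial outcome (technique failure) ends observation of another (survival).

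The Study withdrawal section lists, as condition (iv) for withdrawal, "switching mode to long-term hemodialysis, kidney transplantation, or conservative treatment". It then describes the intention-to-treat approach: "data collected prior to study withdrawal will be considered for participants who discontinue or deviate from the assigned intervention protocols". The Statistical analysis section promises "All analyses will be conducted on both a per-protocol and intention-to-treat basis".

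Table 3 schedules hospitalisation to month 24 and adverse events to month 25, alongside routine PD clinic visits. It has no row for vital status in people who have left PD. The only competing-risk method is the Fine and Gray sensitivity analysis of the primary infection outcome, with competing events "including mode switching to long-term hemodialysis, kidney transplantation, conservative treatment, or death".

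**The concern.** Stopping at PD discontinuation is sensible for infection: someone without a PD catheter is no longer at risk of a PD-related infection. It does not suit death, for which the person remains at risk.

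Leaving PD also happens after randomisation and is plausibly affected by treatment. The Background ties PD-related infection to technique failure and to mortality. If an intervention prevents infections, fewer people in that arm may leave PD, and those who do leave may have a different risk of death. On-PD survival by arm could then differ from survival by arm. Deaths that were never recorded cannot be recovered by any later analysis plan.

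**Working it through.** **1. What the plan's own figures allow.** The plan states no death rate, transfer rate or survival assumption, so there is no survival figure to reproduce. The arm size is 118 and 3 × 118 = 354, as stated. The nearest relevant figure is the 25% all-cause dropout in the sample-size section:

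- per arm: 118 × 0.25 = 29.5
- total: 354 × 0.25 = 88.5

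This is a ceiling at the planned dropout, not an estimate. The article does not define all-cause dropout. It may include deaths (vital status known) and people still on PD who refuse the protocol or use other products.

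**2. Illustration with assumed hazards.** Take constant hazards over T = 2 years: death on PD *m*, transfer off PD *s*, death off PD *k·m*. All three are assumptions: *m* = 0.10 to 0.15 per year, *s* = 0.05 to 0.15 per year, *k* = 1 to 3.

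- Transferred by T: s/(s+m) × [1 − exp(−(s+m)T)]
- Died on PD: m/(s+m) × [1 − exp(−(s+m)T)]
- Transferred and alive at T: s × [exp(−kmT) − exp(−(s+m)T)] / (s+m−km)
- Died after transfer (unrecorded): transferred minus transferred and alive
- Kaplan-Meier mortality censored at transfer: 1 − exp(−mT)

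Worked case, m = 0.10, s = 0.15, k = 3:

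- transferred = 0.6 × (1 − e^−0.5) = 0.236
- transferred and alive = 0.15 × (e^−0.6 − e^−0.5)/(−0.05) = 0.173
- died after transfer = 0.063, or 7.4 of 118
- died on PD = 0.4 × (1 − e^−0.5) = 0.157
- true mortality = 0.157 + 0.063 = 0.220, against a censored estimate of 1 − e^−0.2 = 0.181
- share of deaths missed = 0.0629/0.2203 = 28.6%

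| m | s | k | Transfers per 118 | Deaths on PD | Deaths missed | True 24-month mortality | Censored estimate | Share missed |
|---|---|---|---|---|---|---|---|---|
| 0.10 | 0.05 | 1 | 10.2 | 20.4 | 1.0 | 18.1% | 18.1% | 4.7% |
| 0.10 | 0.10 | 3 | 19.5 | 19.5 | 5.1 | 20.8% | 18.1% | 20.8% |
| 0.10 | 0.15 | 3 | 27.9 | 18.6 | 7.4 | 22.0% | 18.1% | 28.6% |
| 0.15 | 0.05 | 1 | 9.7 | 29.2 | 1.4 | 25.9% | 25.9% | 4.6% |
| 0.15 | 0.15 | 3 | 26.6 | 26.6 | 9.8 | 30.9% | 25.9% | 27.0% |

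Over the full grid, 1.0 to 9.8 deaths per arm are missed (5% to 29%). With k = 1 the Kaplan-Meier estimate is unbiased, but deaths are still lost.

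**3. Fit with the planned dropout.** If the 25% excludes deaths, every transfer count in the grid is below 29.5. If it includes deaths, only the lowest corner comes close: m = 0.10, s = 0.05 gives (10.2 + 20.4)/118 = 26%. There, k = 1 to 3 gives 1.0 to 2.6 missed deaths (5% to 12%).

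**4. Effect on an arm comparison.** Suppose the active arm has 30% fewer transfers, the same death hazard on PD, control s = 0.10 to 0.15, and k = 2 to 3. Taking control minus active:

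- true 24-month mortality: 0.4 to 1.4 percentage points in favour of active
- censored Kaplan-Meier: 0
- crude deaths on PD: −0.5 to −0.9 points, so the active arm shows more deaths because its participants stay under observation longer

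**The case against.** **The stop rule rests on one abstract sentence.** The main text speaks of three-monthly assessment to month 24, the withdrawal section only permits withdrawal on a change of modality, and the full protocol is not shown. The permissive wording is a fair point. However, nothing in the article overrides the abstract, the visits are attached to PD clinic attendance, and the intention-to-treat data are expressly cut at withdrawal. This is a stated rule rather than an omitted detail.

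**Survival is only an example within a safety item.** No survival hypothesis or model is specified, and an on-PD window is a recognised choice for a topical exit-site product. That stands, but the article nowhere says on-PD survival is what is meant. Declaring it would be an acceptable second-best remedy.

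**Stronger readings the documents do not support.**

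- A reader might infer that survival *is* informatively censored. That requires the death risk after leaving PD to differ from the risk on PD. The Background makes this plausible but does not quantify it, and transplant exits may act in the opposite direction.
- A reader might infer that 29 or 30 people per arm will have unknown vital status. Assuming uniform exit, that would be 29.5 of 236 patient-years (12.5%). The undefined dropout figure makes these numbers ceilings, and the article gives no exit pattern.
- A reader might infer that an arm with more transfers will always look safer. That describes crude on-PD death counts. Censored Kaplan-Meier shows no difference in the illustration above.

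**The effect is too small to detect.** At about 20% mortality, the standard error of a difference between two arms of 118 is √(2 × 0.2 × 0.8/118) = 0.052, or 5.2 points, far above 0.4 to 1.4. This stands. The value of the change lies in a complete count of deaths by arm, not in a powered test.

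**Conclusion.** The follow-up rule and the survival outcome do not fit together. As written, deaths after transfer to haemodialysis, transplantation or conservative treatment are not counted, and the Fine and Gray analysis does not help because it concerns infection. That censoring is informative is a reasonable inference, not something the documents establish.

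The size is uncertain: roughly 1 to 10 missed deaths per arm, entirely under assumed hazards, and towards the low end if the 25% dropout already includes deaths. The primary infection outcomes are unaffected. This is a worthwhile, inexpensive improvement to one secondary safety outcome.

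**What to change.** Keep PD discontinuation as the end of infection follow-up. Add that date and cause of death will be recorded to month 24 for every randomised participant unless consent is withdrawn, by hospital record or telephone check. Analyse survival from randomisation on all randomised participants, and reconcile the Abstract, Secondary outcomes and Study withdrawal sections accordingly.

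If this is not possible, name the outcome on-PD survival, treat transfer as a competing event, and report transfers by arm and by destination beside it.

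The cost is a protocol amendment, possibly an ethics or consent check, and some record tracing, with no added visits. At the planned dropout the tracing covers at most about 88 people. Enrolment began in September 2016 and 288 had been randomised by July 2019, so the earliest participants had already passed month 24. For early leavers the check would be retrospective, where consent allows.

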**Discussion:**

The results from this study will provide new clinical and cost-effectiveness evidence to support the best strategy for the prevention of PD-related infections among the Thai PD population.

**Trial registration:**

ClinicalTrials.gov, NCT02547103. Registered on September 11, 2015.

## Background

Peritoneal dialysis (PD) is a well-established treatment modality of home renal replacement therapy (RRT) for end-stage kidney disease (ESKD) patients and has been available in Thailand for more than three decades. Although technical innovations and improvements in PD practice have significantly decreased PD-associated adverse outcomes, PD-related infections, including PD-related peritonitis and exit-site/tunnel infection, are still the most common complications [1–3]. From the patient/caregiver and healthcare professional’s perspectives, PD-related infection is the highest priority outcome in PD treatment [4, 5]. Moreover, PD-related peritonitis is the leading cause of long-term structural and functional peritoneal membrane malfunction [1, 6]. As a result, substantial PD technique failure, hospitalizations, mortality, and healthcare costs are responsible for the limited modality options as an RRT and limited long-term PD use [1–3, 6].

Several strategies involve topical antimicrobial agents to prevent PD-related infections and are being widely used [7]. Of these, daily exit-site care with mupirocin cream or ointment is the most common approach, targeting the exit-site infections caused by *Staphylococcus aureus*. This strategy has been proven to be effective by several existing observational studies, randomized controlled trials (RCTs), and meta-analyses and is recommended by the International Society for Peritoneal Dialysis (ISPD) guidelines [7–13]. Regarding antimicrobial activity, mupirocin is only effective against gram-positive organisms, primarily *S. aureus*. Nevertheless, the emergence of mupirocin resistance has been reported in the long-term application of exit-site care in recent years [14–16].

Chlorhexidine is a water-soluble cationic biguanide with broad-spectrum properties, including antimicrobial effects against gram-positive and gram-negative bacteria, facultative anaerobes and aerobes, and yeast, and it inactivates some viruses [17]. Recently, several controlled trials have revealed that preoperative skin preparation and skin decolonization with chlorhexidine gluconate decreases the rates of surgical-site infections, healthcare-associated infections and bacterial transmission in noncritically and critically ill patients [18–21]. Among PD patients, topical 0.05% to 4% chlorhexidine gluconate aqueous solution, with or without isopropyl alcohol, also commonly has been used in previous practice [22–24] and is recommended by the ISPD guidelines [7]. Chlorhexidine is safe and poorly absorbed through intact adult skin [17]. Nevertheless, the daily application of chlorhexidine gluconate for exit-site care may induce local skin irritation, which could limit patient acceptability and long-term compliance. Whether local irritability limits the long-term and widespread use of chlorhexidine gluconate remains uncertain.

In addition to the ISPD recommendations, two comparative observational studies [25, 26] and one RCT [22] have suggested that exit-site care with normal saline is well tolerated and may be an alternative strategy for the prevention of PD-related infections. The results of these studies revealed that normal saline was not superior or more beneficial than other agents for preventing exit-site infections. However, evidence of exit-site care with normal saline dressing was insufficient and remains unclear.

To date, few RCTs have identified the optimal antimicrobial agent or alternative strategies for the prevention of PD-related infection. Although antimicrobial resistance with routine use is a concern, no RCTs have compared topical antimicrobial agents with usual exit-site care for the prevention of PD-related infections among the Thai PD population. In the COSMO-PD (Chlorhexidine glucOnate verSus Mupirocin Ointment in the prevention of Peritoneal Dialysis-related infection) trial, we aim to assess the safety, efficacy, and cost-effectiveness of a chlorhexidine gluconate-impregnated patch, mupirocin ointment, and usual exit-site care with normal saline dressing in preventing PD-related infections. We hypothesize that the chlorhexidine gluconate-impregnated patch or mupirocin ointment will be superior to usual exit-site care with normal saline in terms of the efficacy and cost utility of the interventions.

## Methods/Design

### Trial design

The COSMO-PD is an active-controlled, double-blinded, multicenter, randomized clinical trial with usual exit-site care. This trial has been registered with ClinicalTrials.gov (NCT02547103). The study protocol was drafted in accordance with the Standard Protocol Items: Recommendations for Intervention Trials (SPIRIT) statement (Additional file 1) [27]. The study flow is illustrated in Fig. 1.

**Fig. 1 Fig1:**
[figure not shown]
Study flow of the COSMO-PD trial

### Trial population and study setting

Adult PD patients, 18 years or older, from three settings in Thailand will be screened for eligibility, including from (i) Nakornping Hospital, Chiang Mai, the largest PD program in Northern Thailand; (ii) Maharaj Nakorn Chiang Mai Hospital, Chiang Mai University, University Hospital of Northern Thailand; and (iii) Songklanagarind Hospital, Prince of Songkla University, University Hospital of Southern Thailand. The inclusion and exclusion criteria are provided in Table 1.

**Table 1 Tab1:** Eligibility criteria of the COSMO-PD trial

Inclusion criteria	Exclusion criteria
• Participants aged 18 years or over at the date of screening • Participants with ESKD who were undergoing PD by either automated peritoneal dialysis or continuous ambulatory peritoneal dialysis	• History of psychological illness or condition that interferes with the ability to understand or comply with the requirements of the study • Recent (within 1 month) exit-site/tunnel infection or PD-related peritonitis • Known hypersensitivity to or intolerance of chlorhexidine or mupirocin • Current or recent (within 1 month) treatment with antibiotics administered by any route • Nasal or exit-site carriage of mupirocin-resistant *S. aureus* or chlorhexidine-resistant *s. aureus*

Abbreviations: *ESKD* end-stage kidney disease, *PD* peritoneal dialysis, *S. aureus Staphylococcus aureus*

### Patient recruitment

We will pre-screen all PD patients for eligibility. The research team will approach all eligible patients at each PD center and identify patients who are interested in participating in the study. After recruitment and informed consent, participants and their caregivers (if available) will undergo screening to determine *S. aureus* colonization. Screening cultures will be performed by trained study team members using standardized methodology by obtaining a nasal swab from participants and their main caregivers. Participants will also be screened for *S. aureus* colonization at the exit site. All sample screening cultures will be analyzed at the Microbiology Laboratory, Faculty of Pharmacy, Chiang Mai University, according to the Clinical and Laboratory Standards Institute guidelines. Recruitment will occur continuously over a 3-year period to meet the target participant population.

### Interventions

All participants will be required to perform daily washings of the exit site with antibacterial soap while showering, followed by drying of the exit site using a sterile gauze pad. Once-daily usual exit-site care dressing with normal saline will be performed for all participants before application of the randomly assigned fixed-order interventions, as follows: (i) chlorhexidine gluconate-impregnated patch plus placebo ointment base or (ii) placebo sterile patch plus mupirocin ointment or (iii) both placebo sterile patch and placebo ointment base. Participants who were *S. aureus* nasal carriers (within 4 weeks in the screening period) will be decolonized with 2% mupirocin ointment applied to both anterior nares twice daily for 5 consecutive days before the trial starts. All medications administered as a part of standard PD care will be allowed. Details of the investigational medicinal products (IMPs) and their administration are provided in Table 2 and Additional file 2: Appendix 1. Participants will record the use of IMPs with adherence, which will be monitored by their return of the relevant packaging (plastic sachets and ointment tubes).

**Table 2 Tab2:** IMPs in the COSMO-PD trial

Intervention	Chlorhexidine gluconate	Mupirocin ointment	Usual care with normal saline dressing
Description of IMPs	Non-ionized cloth impregnated with 2% chlorhexidine gluconate (Ion PAD PLUS CHG2®, Pose Health Care., Ltd.)	2% mupirocin calcium ointment (Charoon Bhesaj Co., Ltd.)	Isotonic solution, 0.9% sodium chloride irrigation USP (A.N.B. Laboratories Co., Ltd.)
Packaging	Non-rinse, disposable, single use in plastic sachet	5-g ointment tube	Plastic bottle container 500 mL, sterile and non-pyrogenic
Dummy placebo	Identical placebo ointment tube	Identical plastic sterile non-ionized patch sachet	Identical both placebo ointment tube and placebo plastic sterile non-ionized patch sachet
Administration	Wiping over PD catheter exit site after dressing with normal saline solution, then applying with placebo ointment base by participants or their caregivers, once daily.	Daily applying to PD catheter exit site by participants or their caregivers after dressing with normal saline and wiping with placebo sterile non-ionized patch, respectively	Daily dressing exit site with normal saline solution by participants or their caregivers, then wiping with placebo sterile non-ionized patch and applying with placebo ointment base, respectively
Duration	Over a 24-month period	Over a 24-month period	Over a 24-month period

Abbreviations: *IMPs* investigational medicinal products, *PD* peritoneal dialysis, *USP* the United States Pharmacopeia

